## Methods

### Study design

This is a retrospective multicentric cohort study conducted at three Swiss Hospitals, Cantonal Hospital of Fribourg (HFR), University Hospital of Geneva (HUG) and University Hospital of Bern (Inselspital), to evaluate the effects of GLP-1 RA therapy on patients with IPMNs. Data from January 2010 to July 2026 will be reviewed.

The primary focus of the study will be to investigate the impact of GLP-1 RA therapy on the progression of IPMNs, specifically examining changes in IPMN radiological characteristics such as described in the Kyoto 2023 Consensus [1]. Additionally, the study will assess the variations in serum tumor markers such as CA19−9 and CEA and incidence of acute pancreatitis in patients undergoing GLP-1 RA treatment. The progression of IPMNs to high-grade dysplasia or invasive carcinoma, the need for surgical intervention or changes in IPMN surveillance protocols will also be assessed.

Data already collected from medical records, laboratory results, and imaging studies will be reviewed for patients diagnosed with IPMNs and treated with GLP-1 RAs for diabetes or obesity between 01.01.2010 and 31.07.2025 at HFR, HUG, and Inselspital. To assess the impact of GLP-1 RA exposure in patients with IPMNs, we will also include control groups without GLP-1 RA exposure and without IPMNs, resulting in four groups defined by a 2 × 2 factorial design (GLP-1 RA exposure: yes/no × IPMN: yes/no) (Fig 1).

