### Data collection

Data will be extracted from electronic medical records and include demographic information (age, sex, BMI), clinical and family history, comorbidities (e.g., diabetes, dyslipidemia, hypertension), laboratory values (HbA1c, fasting glucose, lipase, amylase, CA19−9, CEA), and imaging findings. Study data will be collected and managed using REDCap electronic data capture tools hosted at University of Fribourg [20,21]. REDCap database is available as S2 File. Data collection will start on September 2025 and is expected to be completed by March 2026. Results are expected to be published by November 2026. S3 File illustrates a detailed schedule for enrolment, data collection and assessment.

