#### Positive controls.

Groups need to balanced in age, BMI, and in their number of follow-ups. If age between groups is unbalanced, as defined by a Cohen’s d > 0.4, outliers will be removed until this threshold is reached. For the number of follow-ups, follow-ups above the limiting factor will be ignored from the data collection to balance the groups if needed.

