#### Analysis plan.

H1) We expect significantly more occurrences of change in at least one of the criteria from the Kyoto 2023 Consensus (see Outcomes section) [1] from patients with GLP-1 RA & IPMN than patients with no GLP-1 RA & IPMN, as assessed by a one-sided test of two proportions. H2) We expect significantly greater changes in the CEA (H2a) and CA19−9 (H2b) serum tumor markers over time induced by GLP-1 RA, as assessed by the interaction term of the within-factor Time and the between-factor Group (GLP-1 RA & IPMN vs. no GLP-1 RA & IPMN). H3) We expect significantly different incidence of AP driven by GLP-1 RA and IPMN, as assessed by a Chi-square test across all conditions (GLP-1 RA & IPMN, no GLP-1 RA & IPMN, GLP-1 RA & no IPMN).

Timing of progression: T0 will be defined as the first available follow-up examination for patients with IPMN who were not treated with GLP-1 RAs, and as the first available follow-up examination after initiation of GLP-1 RA therapy for patients with IPMN who received GLP-1 RAs.

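### Capping the number of follow-ups equalises examinations, not time at risk, while the primary comparison has no time term; the data cut-off also needs reconciling

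*Protocol article*

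**What the plan says.** **Follow-up rule.** Protocol article, Positive controls: "Groups need to balanced in age, BMI, and in their number of follow-ups". For the last of these, "follow-ups above the limiting factor will be ignored from the data collection to balance the groups if needed". The limiting factor is not defined, no scan interval is given, and duration of follow-up is not among the quantities to be balanced.

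**Primary comparison.** Analysis plan, H1: "We expect significantly more occurrences of change in at least one of the criteria from the Kyoto 2023 Consensus" in exposed than in unexposed patients with IPMN, "as assessed by a one-sided test of two proportions". The start of observation is fixed: "T0 will be defined as the first available follow-up examination for patients with IPMN who were not treated with GLP-1 RAs", and for exposed patients it is the first such examination after the drug was started. No end of observation is given.

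**Dates.** Study design: "Data from January 2010 to July 2026 will be reviewed"; the Abstract gives the same end. Two paragraphs later, Study design describes the patients whose records are reviewed as diagnosed and treated "between 01.01.2010 and 31.07.2025 at HFR, HUG, and Inselspital". Data collection: "Data collection will start on September 2025 and is expected to be completed by March 2026".

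**Related text.** The Discussion lists as a limitation that late changes may not yet be visible in the available follow-up.

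**The concern.** A proportion of patients who have ever changed rises with the time they are watched. H1 contains nothing that accounts for this, so the comparison is fair only if the two IPMN groups are observed for similar lengths of time. The only control on length of follow-up in the article is the visit cap, and it works on a count. Two patients with the same number of scans can have been followed for quite different periods.

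The cap also has a cost when intervals are equal. If examinations above the limit are ignored, a change first seen on one of them does not count. That is a heavy price with 10 to 20 exposed IPMN patients, and it worsens a limitation the authors already state.

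The date conflict bears on the same analysis: without one cut-off, the end of observation for H1 is undefined.

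**Working it through.** The plan gives no figure of its own on this point: no hazard of progression, no scan interval, no value for the cap. Everything numerical below is illustration.

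**1. Equal visits, unequal intervals.** Let both IPMN groups have the same hazard *h* and the same number of visits *k* after T0, spaced *d* years apart. The proportion changed by the last counted visit is 1 − exp(−h·k·d). With *k* = 3 (assumed):

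| Yearly hazard (assumed) | 6-monthly, 1.5 years | Yearly, 3 years |
|---|---|---|
| 5% | 1 − exp(−0.075) = 7% | 1 − exp(−0.15) = 14% |
| 10% | 1 − exp(−0.15) = 14% | 1 − exp(−0.30) = 26% |
| 15% | 1 − exp(−0.225) = 20% | 1 − exp(−0.45) = 36% |

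The interval ratio drives the result. At a 10% hazard, with yearly scans in one group:

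- 6-monthly scans in the other (ratio 2:1): a gap of 12 points.
- 8-monthly scans in the other (ratio 1.5:1): 1 − exp(−0.20) = 18% against 26%, a gap of 8 points.
- Yearly scans in both: no gap.

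**2. Effect on the H1 test.** Exact binomial enumeration of the one-sided pooled z test at nominal 0.05, with no true effect, 10% yearly hazard, *k* = 3 or 4, and 10 or 20 patients per group:

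| Scan intervals in the exposed group | Rejection rate |
|---|---|
| Same as unexposed | 0.048 to 0.052 |
| Twice as long | 0.15 to 0.28 (n = 10); 0.24 to 0.38 (n = 20) |
| Half as long | 0.001 to 0.009 |

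The bias can therefore go either way: a false signal in one direction, a tendency to hide real harm in the other.

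**3. Progressions lost to the cap.** With yearly visits cut from *K* to *k*, the share of first progressions lost is 1 − [1 − exp(−h·k)] / [1 − exp(−h·K)]. At *h* = 0.10, *K* = 5, *k* = 3 this is 1 − 0.259/0.393 = 34%. Over hazards of 5% to 15% a year, the loss is 31% to 37% for a cut from 5 visits to 3, and 48% to 58% for a cut from 8 to 3.

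**4. Dates side by side.**

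- Data reviewed to July 2026; collection complete by March 2026. The last four months, April to July 2026, cannot be captured.
- 31.07.2025 is attached to the patients diagnosed and treated. It could be an identification window, with a later date for follow-up, but the text does not say so.
- If collection does end in March 2026, at most about eight months after 31.07.2025 are in question.

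**The case against.** **The cap has a rationale.** H1 counts a change in any one of several imaging criteria, so each extra scan is another chance to record a change, including measurement noise. Equal visit counts equalise those chances. This stands. It is why simply dropping the cap and using plain person-year rates or Kaplan-Meier would bring detection bias back, and why the remedy should handle scan timing. It does not make time at risk equal.

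**Nothing shows that intervals differ.** No section suggests that GLP-1 RA users are scanned more or less often. This also stands: it limits what can be said about size, not the gap in the rule.

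**The rule is conditional and loosely worded.** It applies only if needed, and it does not literally say that later examinations are the ones ignored. That is the natural reading, no more.

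**The study is declared hypothesis-generating.** This softens the consequence, but an avoidable bias is still worth removing.

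Four stronger readings may tempt a reader, and the document does not support them:

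- *That visit count follows from progression, so the cap shortens follow-up most in the highest-risk patients.* The protocol lists changes in surveillance as something to be assessed; it does not say that worse lesions are scanned more. The equal-hazard illustration would not describe that case anyway: 20% a year over 1.5 years and 10% a year over 3 years both give 1 − exp(−0.30) = 26%, a masked difference rather than a spurious one.
- *That the 12-point gap is the expected bias.* It rests on an assumed 2:1 interval ratio.
- *That ignored examinations are lost for good.* This is a chart review, and the records remain. Retrieving them later would mean a second abstraction.
- *That a full 12 months of follow-up hangs on the dates.* The stated end of collection limits it to about eight.

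**Conclusion.** The point holds in this form. As written, the rule balances the number of examinations and can leave the two IPMN groups with unequal time at risk, while H1 has no time term and no stated end of observation to correct for it. Where the cap is used, it also discards progression seen on the ignored examinations.

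Size and direction of any bias in H1 cannot be derived from the document. It is zero when intervals are equal. Under the assumed 2:1 ratio it reaches 7 to 16 points (5% and 15% yearly hazard, from the rounded table values). The loss of events from the cap does not need unequal intervals, but its size depends on assumed hazards and visit numbers.

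The date conflict is separate and needs no assumption: a review to July 2026 is incompatible with collection ending in March 2026, and the role of 31.07.2025 is not stated.

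**What to change.** 1. **Positive controls:** remove the cap on follow-ups. Collect every examination from T0 with its date.
2. **Analysis plan, H1:** analyse time from T0 to first change in a Kyoto criterion, censored at last imaging. An interval-censored analysis is preferable, because a change is known only to lie between two scans and the method then accounts for scan timing. A common fixed time window is a simpler alternative. Events per person-year can be given as a plain summary.
3. **Sensitivity analysis:** keep the visit-capped comparison here, where its equal detection opportunities are useful.
4. **Analysis plan, H2:** use all marker values with their actual times in a mixed model, so that no values need be dropped to equalise counts. The article does not say whether the cap extends to laboratory follow-ups.
5. **Abstract, Study design and Data collection:** state one identification window and one data cut-off, the latter no later than the end of data collection.

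The cost is modest extra chart abstraction and a less simple analysis. With 10 to 20 patients per group the time-based estimates will be imprecise and should be reported with confidence intervals. The change is cheapest before collection closes, since it then avoids returning to the charts.

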#### Analysis plan.

H1) We expect significantly more occurrences of change in at least one of the criteria from the Kyoto 2023 Consensus (see Outcomes section) [1] from patients with GLP-1 RA & IPMN than patients with no GLP-1 RA & IPMN, as assessed by a one-sided test of two proportions. H2) We expect significantly greater changes in the CEA (H2a) and CA19−9 (H2b) serum tumor markers over time induced by GLP-1 RA, as assessed by the interaction term of the within-factor Time and the between-factor Group (GLP-1 RA & IPMN vs. no GLP-1 RA & IPMN). H3) We expect significantly different incidence of AP driven by GLP-1 RA and IPMN, as assessed by a Chi-square test across all conditions (GLP-1 RA & IPMN, no GLP-1 RA & IPMN, GLP-1 RA & no IPMN).

Timing of progression: T0 will be defined as the first available follow-up examination for patients with IPMN who were not treated with GLP-1 RAs, and as the first available follow-up examination after initiation of GLP-1 RA therapy for patients with IPMN who received GLP-1 RAs.

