**Methods:**

This retrospective multicentric cohort study will analyse data from January 2010 to July 2026 across three Swiss tertiary institutions. Patients with a radiological diagnosis of IPMN and/or treated with GLP-1 RAs will be included. Patients will be stratified into four groups according to a 2 × 2 design based on GLP-1 RAs exposure and IPMN status. The primary objective is to evaluate the impact of GLP-1 RAs on IPMN progression using radiological criteria from the Kyoto 2023 Consensus. Secondary objectives include assessing changes in tumour markers (CA19−9, CEA), the incidence of acute pancreatitis, the progression of IPMNs to high-grade dysplasia or invasive carcinoma, and the need for surgical intervention or altered surveillance protocols associated with GLP1 RAs use.

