**Fig 1 pone.0357577.g001:**
[figure not shown]
Study design and comparison groups. Schematic overview of the retrospective multicentric cohort study evaluating the impact of GLP-1 RA therapy on patients with IPMNs. Four study groups will be included according to IPMN diagnosis and GLP-1 RA exposure: patients with IPMN treated with GLP-1 RAs, patients with IPMN not treated with GLP-1 RAs, patients without IPMN treated with GLP-1 RAs, and patients without IPMN and without GLP-1 RA exposure (general population). The primary outcome (1) is the progression of radiological IPMN characteristics according to the Kyoto 2023 Consensus criteria. Secondary outcomes include longitudinal changes in serum CA19−9 and CEA levels (2) and the incidence of acute pancreatitis (3). We hypothesize that GLP-1 RA therapy is not associated with an increased progression of IPMN radiological features or adverse pancreatic outcomes compared with patients not exposed to GLP-1 RAs.

A list of patients diagnosed with IPMNs will be compiled (List A), and this group will then be cross-referenced with data from patients who have been treated with GLP-1 RAs (List B). ICD-10 codes, keywords like IPMN and ATC medication codes will be used to identify the patients and compile the two lists (S1 File). This method will allow us to identify the subset of patients in whom both IPMN and GLP-1 RA treatment are present. The same number of patients will be randomly extracted from the two lists. For example, if 3 patients with GLP1-RA and IPMN are extracted in the HFR dataset, then 3 patients will be extracted in List A and 3 in List B. The same procedure will be carried out for the other two institutions. For the no GLP-1 RA & no IPMN group, the proportion of AP will be generalized to the incidence in the general population.

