### Outcomes

#### Primary outcome.

Changes in IPMN radiological characteristics based on criteria from the Kyoto 2023 Consensus [1].

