### Radiological evaluation

MRI is the preferred imaging modality; CT scans will be included if MRI is unavailable. Two senior radiologists at HFR will independently and blinded to prior findings assess imaging studies with the internationally recognized semiological criteria for assessing cystic pancreatic lesions on cross-sectional imaging: high-risk stigmata and worrisome features (cyst diameter, enhancing mural nodules, thickened or enhancing cyst walls, main pancreatic duct diameter, change in calibre, lymphadenopathy, cystic growth). In addition, morphological and signal analysis criteria of the pancreatic gland will be analysed (glandular volume, T1 and T2 weighted signal, diffusion restriction). Furthermore, radiological assessments will be used to monitor for any signs of pancreatitis, such as pancreatic inflammation or fluid collections, that may be associated with GLP-1 RA therapy.

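### The primary outcome and H1 count any change in a Kyoto criterion, in either direction, although the study's stated objective is progression

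*Protocol article*

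**What the plan says.** The protocol article describes one primary outcome in two ways.

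- **As progression.** Abstract, Methods: "The primary objective is to evaluate the impact of GLP-1 RAs on IPMN progression using radiological criteria from the Kyoto 2023 Consensus". Fig 1 caption: "The primary outcome (1) is the progression of radiological IPMN characteristics according to the Kyoto 2023 Consensus criteria". The Study design section names progression as the primary focus, then describes the task as examining changes in radiological characteristics. In the Analysis plan, the rule for T0 is labelled as the timing of progression.
- **As change.** Primary outcome: "Changes in IPMN radiological characteristics based on criteria from the Kyoto 2023 Consensus". Analysis plan, H1: "We expect significantly more occurrences of change in at least one of the criteria from the Kyoto 2023 Consensus", with a pointer back to the Outcomes section.

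H1 compares patients with IPMN on GLP-1 RAs with patients with IPMN not on them, using a one-sided test of two proportions. The Sampling plan expects 10 to 20 patients in the exposed IPMN group and a comparison group of the same size.

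The Radiological evaluation section introduces the features as high-risk stigmata and worrisome features and lists seven items, two of them diameters. It also says "Two senior radiologists at HFR will independently and blinded to prior findings assess imaging studies" and "CT scans will be included if MRI is unavailable".

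**The concern.** H1 is the sentence that turns images into a yes or no per patient, and it sets no direction. A lesion that regresses on one criterion satisfies it as fully as one that worsens. Because the test is one-sided towards more events with the drug, every such regression in an exposed patient is scored as evidence of harm.

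Two errors can follow. If improvement is about equally frequent in both groups, it adds events that say nothing about progression, and a real difference is harder to see. If improvement is more frequent with GLP-1 RA, the study could report a safety signal produced by a favourable effect. In groups of 10 to 20, a few misdirected events can decide the result.

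This is more than detail left to a fuller document. The article does fix the event, and the event it fixes does not match its own objective.

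**Working it through.** **Step 1: compare the wording.**

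| Place | Term for the primary outcome | Direction |
|---|---|---|
| Abstract, Methods | progression | worsening |
| Study design | progression, then changes | mixed |
| Fig 1 caption | progression | worsening |
| Primary outcome | changes | none |
| Analysis plan, H1 | change in at least one criterion | none |
| Analysis plan, T0 rule | progression | worsening |

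Of the seven listed items, only cystic growth is directional by its own name. Cyst diameter and main-duct diameter can move either way, and a nodule, wall thickening or enlarged node can appear or disappear. The two places that govern scoring are the two without a direction.

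**Step 2: no plan figure to reproduce.** The only power statement (80%, alpha 0.05) is for a 2×2 ANOVA, not for H1's test of two proportions. The article gives no rate of progression or improvement. All rates below are assumptions chosen to show the mechanism.

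**Step 3: dilution.** Let *p* be the proportion with true progression and *r* the share of non-progressors who improve on some criterion, equal in both groups. The observed event proportion is *p* + (1 − *p*)*r*, so the observed difference is the true difference × (1 − *r*).

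Assume *p* = 0.10 unexposed and 0.30 exposed. With *r* = 0.20:

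- unexposed: 0.10 + 0.90 × 0.20 = 0.28
- exposed: 0.30 + 0.70 × 0.20 = 0.44
- difference: 0.16 = 0.20 × 0.80

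One-sided power (alpha 0.05, normal approximation) is Φ[(d − 1.645·se0)/se1], with se0 from the pooled and se1 from the separate proportions. For *r* = 0.20 and n = 20 per group:

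- se0 = √(0.36 × 0.64 × 2/20) = 0.152
- se1 = √((0.28 × 0.72 + 0.44 × 0.56)/20) = 0.150
- Φ[(0.16 − 0.250)/0.150] = 0.27

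| *r* | Observed proportions | Difference | Power, n = 10 | Power, n = 20 |
|---|---|---|---|---|
| 0 (worsening only) | 10% vs 30% | 20 points | 29% | 47% |
| 0.10 | 19% vs 37% | 18 points | 22% | 35% |
| 0.20 | 28% vs 44% | 16 points | 18% | 27% |
| 0.30 | 37% vs 51% | 14 points | 15% | 22% |

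**Step 4: improvement more common in the exposed group.** Assume true progression of 10% in both groups, and improvement in 20% of exposed and 5% of unexposed patients, independent of progression.

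- exposed: 1 − 0.90 × 0.80 = 0.28
- unexposed: 1 − 0.90 × 0.95 = 0.145

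Enumerating all outcomes of the one-sided pooled z-test at 0.05, H1 is significant in 17% of studies at n = 10 and 28% at n = 20. On a worsening-only event (10% vs 10%), the same test rejects in 3% and 5%.

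**Step 5: equal improvement does not create false harm.** With 10% progression and a further 5% improving in both groups (15% vs 15%), the rejection rate is 4% at n = 10 and 5% at n = 20. False harm needs improvement that differs by exposure.

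**The case against.** The strongest reply is that the intent is plain. The objective, the figure and the T0 rule all say progression. The criteria are introduced as high-risk stigmata and worrisome features, which are adverse signs, and nothing says that improvement will be scored. Thresholds may be in the full protocol or the data-capture form, which are not shown. The Discussion already concedes information bias and limited power and calls the results hypothesis-generating.

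Much of this stands. Worsening is probably what is meant, and it would be wrong to say the authors intend to count regression as harm. But the sentence that defines the event, and the outcome entry it points to, do not say so. Small numbers and an exploratory purpose do not make regression and progression interchangeable.

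A reader might infer more than the article supports:

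- **That the radiologists know each patient's exposure.** The article states masking to prior findings and is silent on exposure. It does not say the readers are unmasked. Reading without prior findings is itself a protection against anchoring.
- **That CT will be compared with MRI in the same patient.** The Study design section speaks of cases where only CT is available, which more naturally describes CT-only patients.
- **That reading noise over seven items swamps the endpoint.** This needs a per-item error rate the article does not give, and independence between items that overlap, such as cyst diameter and cystic growth. Noise equal in both groups costs power and leaves the one-sided error near 5%.

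**Conclusion.** The point holds for direction. The event in the Primary outcome entry and H1 is undirected, the stated objective is progression, and H1 is tested one-sided for more events with the drug. This should be corrected before images are scored.

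The size cannot be fixed from the article. Under the assumed rates, improvement in 10% to 30% of non-progressors removes 2 to 6 points of a 20-point difference and lowers power at 20 per group from 47% to between 35% and 22%. An improvement rate of 20% against 5% makes H1 significant for harm in 17% to 28% of studies with no difference in progression. If improvement is rare, both effects are small.

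The conclusion does not extend to unmasked readers, mixed-modality comparison or a particular amount of measurement error. Those are unstated in the article, not stated wrongly.

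**What to change.** Define the H1 event as worsening only: new appearance or worsening, relative to T0, of a high-risk stigma or worrisome feature, judged against the Kyoto criteria already cited. Report improvement separately by group. Use the same term in the abstract, Study design, the Fig 1 caption, Primary outcome and H1.

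Two secondary clarifications fit in the same edit. State whether the readers are masked to GLP-1 RA exposure, since only prior findings are mentioned. If any patient has MRI at one time and CT at another, report those pairs as a sensitivity analysis.

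This is a wording change and needs no extra patients, scans or readers. The downside is fewer events. In the illustration with *r* = 0.20 and 20 per group, expected events fall from 20 × (0.28 + 0.44) = 14.4 to 20 × (0.10 + 0.30) = 8. Power still rises from 27% to 47%, because the events removed carry no information on progression, but it remains low.

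### H1 counts any change in a Kyoto imaging criterion as IPMN progression and does not separate changes seen only on scans with signs of pancreatitis, so a positive or negative H1 cannot be cleanly read as neoplastic

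*Protocol article*

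**What the plan says.** All references are to the protocol article.

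- **Outcomes, Primary outcome:** "Changes in IPMN radiological characteristics based on criteria from the Kyoto 2023 Consensus". No condition is set on cause, direction or persistence.
- **Fig 1 caption:** "The primary outcome (1) is the progression of radiological IPMN characteristics according to the Kyoto 2023 Consensus criteria". Change in the criteria is thus read as progression.
- **Analysis plan, H1:** "We expect significantly more occurrences of change in at least one of the criteria from the Kyoto 2023 Consensus" in IPMN patients with GLP-1 RA exposure than in those without, "as assessed by a one-sided test of two proportions". One changed criterion is enough.
- **Radiological evaluation:** the features read are "cyst diameter, enhancing mural nodules, thickened or enhancing cyst walls, main pancreatic duct diameter, change in calibre, lymphadenopathy, cystic growth". The readers work blinded to prior findings. The same section adds that "radiological assessments will be used to monitor for any signs of pancreatitis, such as pancreatic inflammation or fluid collections", and says these signs may be associated with the drug.
- **Analysis plan, H3:** "We expect significantly different incidence of AP driven by GLP-1 RA and IPMN", tested by one Chi-square across three groups.
- **Population:** refusal of consent is the only exclusion.

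**The concern.** H1 and H3 address two questions: whether the drug is linked to faster change in the neoplasm, and whether AP incidence differs. Some of the features read for H1 could plausibly also change with inflammation, for example wall enhancement, duct calibre, nodes, or a collection beside a cyst, and some of these changes may later resolve. This is clinical reasoning; the article does not state it. The article does show that lesion features and pancreatitis signs are assessed in the same imaging evaluation, and that the H1 event is unrestricted. A change seen only on a scan with pancreatitis signs therefore counts by default.

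One AP episode could then enter both hypotheses. An inflammatory effect could be reported as progression of a premalignant lesion, or a lower AP frequency under exposure could mask real progression. In groups this small, a single patient matters.

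**Working it through.** **Is there a separating rule?** The Primary outcome names changes in characteristics, H1 names a change in at least one criterion, and Fig 1 names progression. The Radiological evaluation section records pancreatitis signs but does not connect them to H1. None of these sets aside a flagged scan, requires persistence, or asks readers to attribute a change. The T0 rule fixes only the starting examination.

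**Plan's own figure.** The article gives no event rate and no power for H1. Its only design figure, 80% power for a 2x2 ANOVA, concerns another analysis and does not bear on this point.

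**Inputs from the document.** n = 10 to 20 per IPMN group (Sampling plan); alpha 0.05; one-sided test of two proportions. One patient shifts a group's proportion by 1/20 = 5 points to 1/10 = 10 points.

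**Assumed inputs.** True progression p is the same in both groups (20%, varied from 10% to 30%). The share of patients with an AP-related change in a criterion is a0 (unexposed) and a1 (exposed). The test is the pooled z-test.

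**Formulae.** Event probability per group: P = 1 − (1 − p)(1 − a). Test: z = [(x1 − x0)/n] / √[2·p̄(1 − p̄)/n], with p̄ = (x1 + x0)/(2n), rejecting if z > 1.645. The rejection rate is the exact sum of the two binomial probabilities over all rejecting pairs (x1, x0).

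Example with p = 20%, a0 = 5%, a1 = 10%: P0 = 1 − 0.80 × 0.95 = 0.240 and P1 = 1 − 0.80 × 0.90 = 0.280, a spurious difference of 4 points.

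| a0 vs a1 (p = 20%) | P0 vs P1 | n = 10 | n = 15 | n = 20 |
|---|---|---|---|---|
| 0 vs 0 | 0.200 vs 0.200 | 0.046 | 0.058 | 0.051 |
| 5% vs 5% | 0.240 vs 0.240 | 0.048 | 0.059 | 0.052 |
| 2% vs 5% | 0.216 vs 0.240 | 0.061 | 0.080 | 0.073 |
| 5% vs 10% | 0.240 vs 0.280 | 0.072 | 0.094 | 0.090 |
| 0 vs 10% | 0.200 vs 0.280 | 0.104 | 0.146 | 0.149 |
| 10% vs 5% | 0.280 vs 0.240 | 0.031 | 0.035 | 0.028 |

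Equal shares leave the test near its nominal level. A lower share under exposure makes it conservative.

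**Sensitivity to p.** For 0 versus 10%, the rates at n = 10 and n = 20 are 0.113 and 0.206 if p = 10%, and 0.097 and 0.120 if p = 30%.

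**The case against.** **Silence.** No section says that changes on AP scans count, and attribution rules often sit in a reading manual or an SAP that is not shown. H1 also refers to the Kyoto consensus and the Outcomes section, not directly to the feature list under Radiological evaluation, and that consensus cannot be checked here. This lowers confidence. It does not remove the point, because the article itself fixes the primary event as an unrestricted change and labels it progression.

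**Direction.** A reader might infer that H3 expects more AP under the drug, so that H1 is pushed towards a positive result whenever H3 is true. The documents do not support this. H3 says only that incidence differs, and names IPMN as well as the drug as a driver. It could hold because IPMN patients differ from patients without IPMN, which leaves H1 untouched, since both H1 groups have IPMN. The Fig 1 caption hypothesises no increase in adverse pancreatic outcomes, and the Introduction reports no definitive association with AP in recent meta-analyses. This objection stands.

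**Size.** Assuming no AP-related change in unexposed patients gives the largest effects. These patients also have IPMN, so a non-zero share is at least as plausible, and the inflation is then modest. This stands.

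**Remedy.** Removing pancreatitis scans from the primary count would condition on a post-exposure event. The Introduction lists pancreatitis as a possible route to neoplasia, so lasting change arising that way belongs to the drug's total effect. Dropping it could bias a safety study towards no harm. The Positive controls section may also discard surplus follow-ups, so a confirming scan may be missing. This stands against altering the primary count, but not against a second, prespecified analysis.

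**Conclusion.** The point holds in a limited form. As written, H1 cannot tell neoplastic change from change seen only alongside signs of pancreatitis, and the documents do not show which way, or whether, this biases the result. With 20% true progression and 10 to 20 patients per group, the one-sided rejection rate rises from about 5% to about 6–8% for AP-related change of 2% versus 5%, 7–9% for 5% versus 10%, and 10–15% for 0% versus 10%. With the frequencies reversed it falls below 5%.

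These figures rest on assumed rates, and on the premise that inflammation can alter the listed features. If AP is rare in both groups the effect is small. The article's statement that results are hypothesis-generating limits the consequences but does not settle which hypothesis a positive H1 would generate. The documents do not support a conclusion that H1 will be falsely positive, or that pancreatitis scans must be excluded from it.

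**What to change.** Keep H1 and T0 as stated, and add the following before reads are linked to exposure:

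1. Use the readers' recorded pancreatitis signs to flag each scan.
2. Prespecify a second H1 analysis in which a change counts only if it is present on a scan without pancreatitis signs, whether the same scan or a later one.
3. Tabulate by group, beside H3, the changes seen only on flagged scans.
4. State that a positive H1 will be interpreted as neoplastic progression only if the two analyses are consistent.

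The cost is a few sentences and one small table. The scans, the readers and the pancreatitis signs are already in the plan. The downside is that genuine progression first seen with pancreatitis and never re-imaged, or whose later scan is dropped to balance follow-ups, leaves the second analysis. It stays in the main one.
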